### Patient-reported outcomes (PROs)

In 2006, the U.S. Food and Drug Administration (FDA) proposed the term patient-reported outcome measures (PROMs) for all measures that can best, or only, be assessed by asking the patients [30]. PROs denote an umbrella term covering the patient’s perspective on physical and psychological wellbeing, symptoms, and treatment effects [31], hence supplement clinical observations. The recognition of PROs as independent outcomes is consolidated by the Consolidated Standards of Reporting Trials (CONSORT) PRO extension statement [32] developed to improve the reporting of PROs.

Performance status and tumor burden are important predictive factors for effect of chemotherapy and survival, and closely linked to symptom burden and patient wishes. Thus, a patient-centered focus with systematic evaluation of PROs and preferences should be part of any treatment, to optimize care, particularly so as tumor-directed treatment becomes less efficient or is discontinued. Nevertheless, it is well documented that systematic symptom assessment is not routine in oncological care [33–35], although frequently used in clinical trials due to the FDA requirements [36]. Unsystematic use of PROs may in part explain inadequate symptom management. This applies to pain as well as other physical and psychological symptoms that are highly prevalent among patients with cancer, such as appetite loss, constipation, dyspnea, fatigue, anxiety, depression, and overall QoL.

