### Study population

#### Inclusion criteria: participant level

##### Patients

At the second level of the C-RCT, the following eligibility criteria apply to patient inclusion:
A verified metastatic or locally advanced cancer of the upper gastrointestinal (GI) tract, lower GI tract, pancreas, liver, breast, bladder, prostate, kidney, cholangiocarcinoma, or malignant melanoma;Defined as a patient in need of PC with an anticipated life expectancy of < 12 months;Scheduled to start the anticipated last line of chemotherapy (definition: tumor directed systemic therapy). Time of inclusion that is based on the decisions about last line of chemotherapy, varies by diagnosis, and is equivalent to first line in some diagnoses;Age > 18 years;Fluency in written and oral Norwegian;Physically and cognitively able to provide written consent, based on clinical criteria, e.g. not too frail or having signs of disorientation, confusion, attention deficit, poor coordination;Scheduled to receive all oncological and specialized palliative treatment at the participating hospital, i.e. residing in the local area of the including hospital;WHO performance status 0–2.

Because gynecological and lung cancer patients receive anticancer treatment at the departments of lung and gynecology in most hospitals, these diagnoses were not included.

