### Data collection and statistics

#### Data registration by study personnel

##### Patients

An e-CRF, developed by the Unit for Applied Clinical Research at NTNU, is used for registration of clinical data, every other month until death or for 1 year. This is the responsibility of the study nurses and Principal Investigators at the participating sites. The first questions of the initial CRF contain confirmation of written informed consent and whether the caregiver can be asked to participate. These items are not replicated in subsequent registrations. The clinical variables are: height; weight; cognition (date, time, day, backwards spelling); co-morbidities; principal cancer diagnosis and date of diagnosis; stage; presence; site and number of metastases; previous and present anticancer treatment (within the past 2 weeks); Karnofsky Performance Status (KPS) score [80]; regular use of medication; current use and dosage of opioids; and the following biomarkers if within the past 7 days: C-reactive protein; hemoglobin; leukocytes; thrombocytes; albumin; GT (Gamma-glutamyltransferase); LD (Lactate-dehydrogenase); creatinine; and contact with the community healthcare services and general practitioner. The same set of variables are registered during follow-up, supplemented with detailed registrations of all anticancer treatment, other medical interventions, change of medication, imaging (X-ray, MRI, CT and PET scans), transfusions, and more administrative data, such as department category for treatment, i.e. palliative or general oncology unit, in- or outpatient status, and emergency or other hospital admissions.

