##### Statistics

The design makes it possible to evaluate the effect of an early integration of oncology and PC at the institutional and patient levels across intervention and control arms, by comparing the use of chemotherapy in the last 3 months of life.

Analyses on the primary outcome will be performed when there are 300 patients in each arm with data on chemotherapy use in the last 3 months of life, which is the basis for the power estimation. Standard descriptive statistics will be used for background variables. Further, data will be analyzed by the intention-to-treat approach; mixed effect regression models will be used to analyze both primary and secondary endpoints in order to account for clustering. Logistic and linear regression models will be used respectively for binary and continuous outcomes and all models will be adjusted for potentially relevant baseline covariates at patient level, i.e. sex, age, diagnosis, performance status score, and baseline symptom scores. The analysis of the main outcome will also be adjusted by size of the catchment areas, which is the randomization stratification factor.

Survival analysis methods, i.e. Kaplan–Meier curves and Cox proportional hazards models with shared frailty terms to account for clustering and Kaplan–Meier curves, will be employed in order to model time to death. Sensitivity analyses to different methods will be applied to handle missing data in the secondary PROs: complete case analysis and multiple imputations. This also applies to patient- and caregiver-reported outcomes. Paper forms will be used to collect medical data and PROs for comparisons across arms.

Further, a potential effect of the intervention at each of the centers in the intervention arm may be evaluated at a later stage as an explorative outcome by comparing post-intervention data with historical data, e.g. on use of chemotherapy and number of readmissions/emergency admissions in the very last stages of life as appropriate.

The CONSORT recommendations for reporting RCTs will be followed. The CONSORT recommendations for reporting C-RCTs will be followed. IBM SPSS Statistics for Windows, version 25.0 (IBM Corp., Armonk, NY, USA) and STATA (Stata Corp. LCC, College Station, TX, USA) will be used.

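### The closed covariate list has no direct measure of disease extent, although the protocol names tumour burden as an important predictive factor and records metastases at baseline

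*Protocol article*

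**What the plan says.** The Statistics section specifies mixed-effects logistic and linear models and states that "all models will be adjusted for potentially relevant baseline covariates at patient level". The covariates follow after an i.e.: "sex, age, diagnosis, performance status score, and baseline symptom scores". The main outcome is also adjusted for size of catchment area, the stratification factor. The Sample size section refers the reader to this list as the full one, so it reads as closed.

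The Background, under Patient-reported outcomes (PROs), says: "Performance status and tumor burden are important predictive factors for effect of chemotherapy and survival, and closely linked to symptom burden and patient wishes".

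Under Data registration by study personnel (Patients), the initial CRF includes "principal cancer diagnosis and date of diagnosis; stage; presence; site and number of metastases". It also records previous and present anticancer treatment, with a two-week window in parentheses.

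The patient inclusion criteria require metastatic or locally advanced disease, an anticipated life expectancy below 12 months, and a planned start of the anticipated last line of chemotherapy. The timing of that line "varies by diagnosis, and is equivalent to first line in some diagnoses".

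**The concern.** The protocol names two factors together as important. It adjusts for one of them directly and for the other only through correlates, although direct measures of the second are collected. It gives no reason.

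The design makes this worth attention. Twelve hospitals are randomised in three strata of catchment size, so nothing in the allocation balances disease extent at patient level. Patients are enrolled after their hospital's arm is known, in a trial described as non-blinded. Two entry criteria rest on clinical judgement: the anticipated last line and the anticipated life expectancy. Physicians in the intervention hospitals complete a programme that covers prognostication before enrolling anyone, and control-arm participants get access to that material only after study closure. Disease extent at entry could therefore differ between arms by chance, or because the two groups of physicians select patients differently.

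The primary outcome is receipt of chemotherapy in the last 3 months of life among patients who are starting a line of chemotherapy. How soon death follows that start affects whether the event occurs. Disease extent, as a predictor of survival, can therefore reach the primary comparison, and it bears directly on the exploratory survival comparison.

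**Working it through.** **1. The plan's own figure (Sample size, Table 2)**

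Inputs from the protocol: 20% v 45%, two-sided 5%, 80% power, 6 hospitals per arm, ICC 0.08, r_adj 0.1.

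- Individually randomised size per arm: n = (t(0.975, 10 df) + z(0.80))² × [0.20 × 0.80 + 0.45 × 0.55] / 0.25² = 61.44.
- With adjustment: 61.44 × (1 − 0.1²) = 60.83.
- Patients per hospital: m = 60.83 × 0.92 / (6 − 60.83 × 0.08) = 49.4, rounded up to 50.
- Per arm: 6 × 50 = 300, as stated.

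The same formula gives all 20 cells of Table 2 within 3%, 18 of them exactly.

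Power at 300 per arm and ICC 0.08, by the joint correlation between covariates and outcome:

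| r_adj | none | 0.1 | 0.2 | 0.3 | 0.4 |
|---|---|---|---|---|---|
| Power | 79.7% | 80.1% | 81.4% | 83.6% | 86.6% |

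The chosen size needs only r_adj = 0.1, so it does not depend on adding disease extent.

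**2. Standard error of the planned difference**

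300 per arm, hospitals of 50, ICC 0.08:

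SE = √[0.4075 × (1 + 49 × 0.08) / 300] = √[0.4075 × 4.92 / 300] = 0.0818, or about 8.2 points.

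**3. Chance imbalance in a disease-extent marker**

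The document gives no prevalence, ICC or effect for such a marker. Assumed here: a binary marker with 40% prevalence (variance 0.24), hospital ICC 0.02 to 0.10, and a 20-point difference in event risk before any other adjustment. The calculation is on the risk-difference scale, as an approximation to the planned logistic model.

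- SD of imbalance = √[2 × 0.24 × (1 + 49 × ICC) / 300]
- Shift at 1 SD = 0.20 × SD
- Share of variance = (shift / SE)²

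| Marker ICC | SD of imbalance | Shift at 1 SD | Shift / SE | Share of variance |
|---|---|---|---|---|
| 0.02 | 5.6 points | 1.1 points | 0.14 | 1.9% |
| 0.05 | 7.4 points | 1.5 points | 0.18 | 3.3% |
| 0.10 | 9.7 points | 1.9 points | 0.24 | 5.6% |

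Removing 1.9 to 5.6% of the variance lowers the standard error by about 1 to 3% (1 − √0.981 and 1 − √0.944). With a 30-point effect the variance share would be about 4 to 13%.

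These are upper figures for the assumed effect. Diagnosis, performance status, symptoms, age and sex are already in the model and absorb part of it.

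**4. Differential enrolment**

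This would be a true bias, but the document gives nothing from which to calculate its size.

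**The case against.** The strongest objection is that chance imbalance between randomised hospitals is sampling variance, not bias. Between-hospital case mix is part of what the planned ICC of 0.06 to 0.09 and the mixed model already carry into the standard error. This stands. For chance imbalance, the gain from adjustment is the modest precision gain shown above.

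Second, the Background sentence explains why patient-reported outcomes matter. It concerns effect of chemotherapy and survival, not receipt of chemotherapy near death, and it promises no adjustment. It also links tumour burden to symptom burden, which is in the model. This stands too: there is no contradiction between passages, and a good part of disease extent is adjusted for indirectly. The same sentence links performance status to symptoms, however, and the plan still adjusts for performance status separately.

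Third, every patient has metastatic or locally advanced disease, which narrows the spread of stage. That is true, but locally advanced v metastatic disease, and the number and site of metastases, still vary.

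Fourth, line of treatment at entry follows diagnosis to a large extent, and diagnosis is a covariate. The e-CRF description may also limit previous treatment to the past two weeks, and number of lines is not listed. So previous treatment cannot be assumed to be available as a covariate.

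A reader might infer that performance status is the only adjustment and that case mix is left uncorrected. The list does not support that. A reader might also take a 10 to 20 point imbalance as typical, giving a shift of 2 to 4 points, or 8 to 16% of the planned 25. A 20-point imbalance is 3.6, 2.7 and 2.1 SD at the three assumed ICCs, outside the 95% range each time.

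**Conclusion.** The point holds as a modest one. The list is closed and contains no direct measure of disease extent, although the protocol calls tumour burden important and collects suitable variables at baseline.

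For chance imbalance the effect is small: about 1 to 2 points at 1 SD against a standard error of about 8, and at most about 2 to 6% of the variance. This rests on the assumed 40% prevalence, 20-point effect and ICC of 0.02 to 0.10. The sample size and planned power are not in question.

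The better reason for the change is differential enrolment, given unblinded recruitment after allocation on judgement-based criteria and prognostication training in one arm. That is a risk and not an observed imbalance, its size cannot be derived from the document, and adjusting for recorded metastases would protect against it only in part. The survival comparison is exploratory and the article lists no covariates for the Cox model, so no separate fault is found there.

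**What to change.** Add one baseline disease-extent covariate to the primary model in the Statistics section: the number of metastatic sites, with locally advanced disease coded zero, taken from the metastasis fields of the initial e-CRF. Use the same covariate in the Cox model if that model is adjusted. Add previous lines of treatment only if the baseline e-CRF records them beyond the two-week window.

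Fix this in writing before outcome data are analysed, because a covariate added after an imbalance has been seen looks post hoc. In a logistic model each added covariate also alters the conditional odds ratio being estimated, which is another reason to settle the list beforehand.

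The cost is one sentence in the plan and 1 to 2 extra model parameters. No new data collection is needed for the metastasis variable.

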### Sample size

Sample size calculation was based on the primary endpoint: the proportion of patients who receive chemotherapy during their last 3 months of life (Table 1). This took into consideration the predetermined number of 12 as the total number of clusters, i.e. hospitals, that was chosen for contingency/feasibility reasons and allowing for intra-cluster correlation coefficient (ICC) in the range of 0.06–0.09, which is usually considered appropriate for process outcomes. In addition, calculations were performed to provide 80% power at the two-sided 5% level to detect a 25% difference in chemotherapy use between the two arms, i.e. 20% versus 45% in the treatment and control groups, respectively [61]. The choice of the clinically relevant treatment effect used for sample size calculation (25% difference for chemotherapy administration) was based on both clinical judgment and previous data [62, 63]. Effects on power increase due to adjustment by baseline measurements and other covariates (see statistical analysis section for the full list of covariates proposed) were also considered, allowing for correlation coefficient between outcome and adjustment covariates (r_adj_) up to 0.4. Table 2 reports sample size per treatment arm for various values of ICC and (r_adj_).

**Table 2 Tab2:** Sample size per treatment arm for various values of ICC and (r_adj_)

			**r**_**adj**_		
	*0.4*	*0.3*	*0.2*	*0.1*	*NO*^a^

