**ICC**					
*0.06*	102	120	138	150	150
*0.07*	126	150	180	198	204
*0.08*	156	204	258	**300**^b^	312
*0.09*	210	318	468	630	714

*ICC* intra-cluster correlation coefficient, *r*_*adj*_ correlation coefficient between outcome and adjustment covariates

^a^No adjustment for baseline covariates

^b^Required no. of patients per arm

A sample size of 300 patients in each arm, with a total of 600 patients, was chosen as it accounts for an ICC up to 0.08 even with a low r_adj_ (no less than 0.1) and for an ICC up to almost 0.09 in case of r_adj_ no less than 0.3. Due to an expected attrition rate up to 12%, 340 patients per arm (680 in total) will be enrolled.

The 12 hospitals were grouped into three strata according to size of catchment area, to decrease the chance of imbalance in cluster characteristics between trial arms. Each cluster consisted of four hospitals: small (69,000–136,000 inhabitants); medium (169,000–282,000 inhabitants); and large (300,000–492,000 inhabitants) (Table 3). This procedure is considered a reliable and easy to measure proxy for other cluster characteristics, potentially impacting on the study outcome. Effect of the variability in cluster size (mean 50, SD 19.5, CV [Coefficient of variation] = 0.39) was calculated through the approach proposed by Van Breuckelen [64]. For CV = 0.39, this method indicates low inflation factors which are in the range of 2.8%–2.2%, for ICC in the range of 0.06–0.09, respectively [64]. The role of the correlation coefficient in sample size formula for binary outcomes and when adjusting for baseline factors is explained by Hemming et al [65]. Sample size calculations in Table 2 were undertaken using the module clustersampsi [65] implemented in the statistical package Stata (Stata Statistical Software, Release 14, Stata Corp., College Station, TX, USA).

**Table 3 Tab3:** Presentation of stratification, randomization results, and sample size at cluster level

Intervention arm				Control arm			
Hospital	Stratification	Inhabitants	Patients	Name	Stratification	Inhabitants	Patients
Stavanger University Hospital, Stavanger	1	352,650	85	Akershus University Hospital, Nordbyhagen	1	490,000	85
Oslo University Hospital	1	340,000	85	St. Olavs Hospital/Trondheim University Hospital, Trondheim	1	300,000	85
Østfold Hospital Trust, Grålum	2	282,600	50	Sørlandet Hospital, Kristiansand	2	170,000	50
Vestfold Hospital Trust, Tønsberg	2	233,000	50	Telemark Hospital Trust, Skien	2	169,000	50

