#### Randomization, blinding, and study monitoring

Randomization was performed within each stratification group using a web-based randomization system developed and administered by the Unit for Applied Clinical Research, Institute of Cancer Research and Molecular Medicine, Norwegian University of Science and Technology (NTNU), Trondheim, Norway. The procedure was concealed for all study personnel. The allocation of hospitals to the intervention and control arms is shown in Table 3.

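### Secondary-outcome models omit the catchment-size strata within which hospitals were randomised, which costs precision wherever stratum is prognostic

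*Protocol article*

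**What the plan says.** The Sample size section describes the stratification: "The 12 hospitals were grouped into three strata according to size of catchment area". It gives the reason: "This procedure is considered a reliable and easy to measure proxy for other cluster characteristics, potentially impacting on the study outcome". The section on randomisation, blinding and monitoring confirms that the strata were used: "Randomization was performed within each stratification group using a web-based randomization system". Table 3 shows the result: two hospitals per arm in each of the three strata, with 85, 50 and 35 planned patients per hospital.

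The Statistics section then makes three statements about the models:

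- Clustering is handled for all endpoints: "mixed effect regression models will be used to analyze both primary and secondary endpoints in order to account for clustering".
- The common covariate set is at patient level: "all models will be adjusted for potentially relevant baseline covariates at patient level, i.e. sex, age, diagnosis, performance status score, and baseline symptom scores".
- The strata are added for one outcome: "The analysis of the main outcome will also be adjusted by size of the catchment areas, which is the randomization stratification factor".

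For time to death, which Table 1 classes as explorative, the plan names "Cox proportional hazards models with shared frailty terms to account for clustering" and no stratum term.

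**The concern.** The covariate list for all models is closed and restricted to patient-level variables, so a hospital-level stratum is not in it. The next sentence adds the stratum for the main outcome and nowhere else. An analysis plan that follows this text would leave the strata out of the models for chemotherapy cycles and timing, other medical interventions, patient-reported outcomes and caregiver-reported outcomes.

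Stratified randomisation with two hospitals per arm in each stratum keeps differences between strata out of the treatment contrast. If the model has no stratum term, those differences stay in the estimated between-hospital variance and inflate the reported standard error. With only 12 clusters, and a sample size set on the primary endpoint alone, what is at stake is avoidable loss of precision on the secondary outcomes and a greater chance of missing a real difference. The article gives no reason why hospital size would matter for chemotherapy use in the last 3 months but not for the other outcomes.

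**Working it through.** **The plan's own figure.** The article gives no standard error for any secondary outcome. Its only related figure is 300 patients per arm (Table 2, ICC 0.08, r_adj 0.1), which reproduces with 6 clusters per arm and a t quantile on 10 df:

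- n_I = (2.228 + 0.842)² × (0.20×0.80 + 0.45×0.55) / 0.25² × (1 − 0.1²) = 61.44 × 0.99 = 60.83
- cluster size = 60.83 × 0.92 / (6 − 60.83 × 0.08) = 49.4, rounded up to 50
- 6 × 50 = 300 per arm

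The same formula matches 18 of the 20 cells of Table 2 exactly. The point does not touch this figure. It does show that 10 df is a reasonable reference for a model without strata; two stratum terms leave 8.

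**Effect on interval width.** Let R² be the share of variance between observed hospital means that stratum explains. This is an assumption; the article does not give it.

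Half-width with stratum / half-width without = √(1 − R²) × t(0.975, 8) / t(0.975, 10) = √(1 − R²) × 2.306/2.228 = √(1 − R²) × 1.035

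| R² | Ratio | Change in half-width |
|---|---|---|
| 0 | 1.035 | 3.5% wider |
| 0.2 | 0.926 | 7% narrower |
| 0.3 | 0.866 | 13% narrower |
| 0.4 | 0.802 | 20% narrower |

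Break-even: R² = 1 − (2.228/2.306)² ≈ 0.07.

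**Dependence on the ICC.** Observed hospital means also carry patient sampling error. With total variance 1 and 50 patients per hospital, the variance of a hospital mean is ICC + (1 − ICC)/50: 0.0984 at ICC 0.08, 0.0396 at 0.02 and 0.0298 at 0.01. For R² of 0.2, 0.3 and 0.4, stratum must therefore explain this much of the true between-hospital variance:

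- ICC 0.08: about 25, 37 and 49%
- ICC 0.02: about 40, 59 and 79%
- ICC 0.01: about 60, 89 and over 100% (impossible)

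Conversely, suppose stratum explains 25% of the true between-hospital variance. At ICC 0.02, R² = 0.25 × 0.02/0.0396 = 0.126 and the net gain is about 3%. At ICC 0.01, R² = 0.25 × 0.01/0.0298 = 0.084 and the net gain is about 1%.

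**Simulation.** A continuous secondary outcome was simulated for 12 hospitals in three strata, two per arm per stratum, with 75, 44 and 31 evaluable patients per hospital (Table 3 sizes × 0.88). A REML model with a random hospital effect was fitted with and without stratum, 4,000 runs per setting. The share is of true between-hospital variance. Tests use t on 10 df without stratum and on 8 df with it.

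| ICC | Share | SE without / SE with | SE without / true SD | Type I without | Type I with | Power, 0.4 SD, without | Power with |
|---|---|---|---|---|---|---|---|
| 0.08 | 0% | 1.00 | 0.98 | 0.048 | 0.048 | 0.50 | 0.48 |
| 0.08 | 25% | 1.15 | 1.13 | 0.030 | 0.051 | 0.50 | 0.58 |
| 0.08 | 50% | 1.36 | 1.30 | 0.015 | 0.052 | 0.46 | 0.70 |
| 0.08 | 75% | 1.70 | 1.63 | 0.002 | 0.045 | 0.44 | 0.86 |
| 0.04 | 0% | 1.00 | 0.97 | 0.051 | 0.050 | 0.71 | 0.69 |
| 0.04 | 25% | 1.12 | 1.09 | 0.033 | 0.046 | 0.71 | 0.76 |
| 0.04 | 50% | 1.26 | 1.23 | 0.015 | 0.039 | 0.73 | 0.85 |
| 0.04 | 75% | 1.46 | 1.43 | 0.007 | 0.035 | 0.73 | 0.93 |

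In no setting did leaving out the strata make the standard error too small. Binary outcomes and the Cox model were not simulated.

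**The case against.** A reader might infer that every secondary standard error is wrong. The article does not support that. With no stratum effect the standard error is right and adjustment slightly lowers power. The stated rationale is hedged, speaks of a single study outcome, and sits in a section built on the primary endpoint. It does not say that catchment size predicts PHQ-9, QLQ-C15-PAL, SF-36 or FAMCARE scores. The ICC range of 0.06 to 0.09 is justified for process outcomes, and none is given for patient- or caregiver-reported outcomes. If those ICCs are low, the gain may be only a few per cent. The patient-level covariates may also absorb part of any difference between strata, so only the remaining share counts. All of this stands and limits the size.

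A reader might also infer that the secondary analyses ignore the cluster design, or that false positives are at risk. Neither follows: mixed models and shared frailty handle clustering, and the error is in the conservative direction.

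Finally, the article condenses a fuller plan, and it does not expressly exclude the strata from other models. An analysis plan not shown here may include them. But the article does more than stay silent: it sets one covariate list for all models and a further adjustment for the main outcome. As written, that is the narrower rule.

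**Conclusion.** The point holds as a conditional loss of precision. The secondary models, and the exploratory Cox model, omit a factor that restricted the randomisation and that the authors themselves thought might matter. Where stratum explains residual between-hospital variance, the intervals are too wide and the tests conservative. The gain from including it is about 7 to 20% of interval width if stratum explains 20 to 40% of the variance between observed hospital means, and about 1 to 3% at an ICC of 0.01 to 0.02 if it explains a quarter of the true between-hospital variance. These shares and the low ICCs are assumptions. The interval formula also assumes equally precise hospital means and t-based inference on 10 or 8 df. The primary analysis, the sample size and the false-positive risk are not affected. This is a modest point, worth correcting because the possible gain exceeds the small fixed cost.

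**What to change.** State in the Statistics section that the three-level catchment-size stratum is a fixed effect in all primary and secondary mixed models, and that it enters the exploratory Cox model as a covariate or as a stratum. The choice between the two for the Cox model is a preference.

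The cost is one sentence and two hospital-level degrees of freedom per model, or about 3.5% in interval width for an outcome unrelated to catchment size. No new data are needed and the sample size stays as it is.

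The change should go with a small-sample reference distribution. With a critical value of 1.96, the simulated type I error of the stratum-adjusted test was 0.067 to 0.092. That comes from having 12 clusters, since the unadjusted model also showed 0.076 to 0.078 when stratum had no effect. The article names no degrees-of-freedom method; the analysis plan may settle it, and it is not counted here as a fault.
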